## Materials and methods

### Participants

A single arm study will be conducted among children aged 3 to 5 years attending Anganwadi centers in SRM UBA adopted villages who will be screened for neurodevelopmental disorders with parental consent. Those identified with NDD or previously diagnosed with any form of NDD will be included in the study.

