The model center, or specialist outreach center, is envisioned to have trained physiotherapists for children's rehabilitation, with pediatric physicians visiting the centers for progress checks and further evaluations. Equipped with essential tools such as swiss ball, peanut ball, obstacle for gait training, balance boards,etc., the center will provide pediatric rehabilitation and group therapies for children. Discussions and arrangements will be initiated with village authorities to position the model center close to or within school/Anganwadi premises.

Subsequent to NDD identification in children, baseline assessments of NDD will be conducted alongside qualitative assessment of caregivers' perspectives and experiences regarding accessing rehabilitation services in the community. Quantitatively, caregiver burden will be evaluated using a caregiver burden scale.

Upon enrollment, children will undergo physiotherapy rehabilitation for one year under a trained physiotherapist, with routine screenings by pediatricians. The neurodevelopmental rehabilitation will include sensorimotor training, motor learning, sensory integration, motor training and neurodevelopmental therapy which will be tailored according to the individual’s needs and the severity and type of disorder. Treatment will be given in person, in group or as individual therapy. The entire timeline and flow have been illustrated in Table 1.

**Table 1 Tab1:** Spirit timeline for the study

	Enrolment and allocation		Post allocation				Endline evaluation	Close-out
Time point	− t1	t0	t1	t2	t3	t4	t5	t7
Preliminary screenings	X							
Parental consent	X							
Analysis of prevalence	X							
Eligibility screen		X						
Obtained signed parental consent		X						
Allocation		X						
Baseline assessments		X						
Establish model centre		X						
One year rehabilitation			X	X	X	X		
Routine follow up screenings by pediatricians			X	X	X	X		
Baseline tools	X	X					X	
Effectiveness of intervention		X					X	
Caregiver burden		X					X	
Data entry and analysis	X						X	
Share findings with authorities	X							X
Final reports								X
Plan future studies								x

Each t indicates 3 months of time span

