Treatment dose, intensity and sessions will be modified based on functional goals. After the year-long intervention, children and caregivers will undergo an end-line evaluation to gauge the effectiveness of the specialist outreach/model clinic in improving children with NDD and alleviating caregiver burden which will be assessed by the Physiotherapist who provided rehabilitation.

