## Statistical analysis

The collected data will be entered into a database and analyzed using SPSS. Baseline demographics including participant details, obstetric history, educational status, family history and other relevant details will be visualized using Tableau. Baseline characteristics will be summarized as frequencies and percentages for categorical variables and as means ± standard deviations (or medians with interquartile ranges for non-normally distributed data) for continuous variables. Inferential statistics: Chi-square test: We will use this to analyze associations between categorical variables, such as caregiver burden severity and prior diagnosis of neurodevelopmental disorders (NDD). t-test: Applied to compare means between two groups, such as pre- and post-intervention caregiver burden scores.

ANOVA: Used to compare differences in continuous outcomes, such as caregiver burden scores and child developmental outcomes, across multiple groups (e.g., different clinics or geographic regions).

Regression analysis: Binary Logistic Regression: This will help us identify the impact of the intervention on the binary outcome (reduction in caregiver burden, yes/no), controlling for potential confounding variables (e.g., socioeconomic status, severity of NDD).

Visualization tools: Tableau will be used to create dashboards summarizing key indicators, such as clinic utilization, caregiver burden trends, and regional prevalence rates.

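### In this single-arm study the planned logistic regression has no intervention term, so it cannot give a confounder-adjusted impact of the centre on caregiver burden

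*Protocol article*

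**What the plan says.** All references are to the protocol article.

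- **Design (Participants):** "A single arm study will be conducted among children aged 3 to 5 years attending Anganwadi centers in SRM UBA adopted villages". On who enters: "Those identified with NDD or previously diagnosed with any form of NDD will be included in the study".
- **Exposure (Procedures):** "Upon enrollment, children will undergo physiotherapy rehabilitation for one year under a trained physiotherapist". No untreated, delayed-start or historical comparison group is described.
- **Timing (Table 1):** caregiver burden is assessed at t0 and t5 only.
- **Regression (Statistical analysis):** the binary logistic model is introduced with "This will help us identify the impact of the intervention on the binary outcome (reduction in caregiver burden, yes/no), controlling for potential confounding variables". The covariates given as examples are socioeconomic status and severity of NDD.
- **Other analyses (Statistical analysis):** a t-test is planned for burden scores before and after the intervention. ANOVA is planned across groups such as clinics or regions. Clinic utilization appears as an indicator for dashboards.

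**The concern.** The stated purpose of the regression does not fit the stated design. To estimate the impact of an intervention, a model needs a variable that separates people by their exposure to it. Here everyone analysed has the same exposure, and the yes/no outcome has already used up the before-after contrast.

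Caregiver burden is the primary outcome, and the centre's impact on it is a primary objective. This regression is the only covariate-adjusted analysis of that outcome that the article describes. Any odds ratio or fitted proportion reported from it under its present description would look like an effect of the centre with confounding dealt with. The Discussion expects the results to guide government agencies and to serve as a pattern for centres elsewhere in Tamil Nadu, so the label matters beyond the paper itself.

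**Working it through.** The article gives no figure for this model, so there is none to reproduce. The check is whether the stated effect can be identified.

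**Inputs.** One arm (Participants). All enrolled children treated (Procedures). Burden B measured at t0 and t5 (Table 1). Outcome is reduction yes/no, with covariates socioeconomic status (SES) and severity (Statistical analysis).

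**1. The model as described.** For caregiver i, let Y = 1 if B(t5) < B(t0), and let T be the intervention indicator:

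logit Pr(Y = 1) = b0 + b1·T + b2·SES + b3·Severity

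In a single-arm study T = 1 for all, so this becomes

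logit Pr(Y = 1) = (b0 + b1) + b2·SES + b3·Severity

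Replace (b0, b1) by (b0 + c, b1 − c). The sum, and so the likelihood, is the same for every c. The data determine b0 + b1 but not b1.

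**2. Rank check.** The design matrix [1, T = 1, SES, Severity] was built with simulated covariates at assumed sizes n = 50, 100 and 200. Each time it had 4 columns and rank 3. The shortfall, 4 − 3 = 1, is the intervention column, which duplicates the intercept. More caregivers do not change this.

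**3. Can time serve as the exposure?** No. Y is computed from both B(t0) and B(t5). There is one Y per caregiver, so no row can be labelled before or after.

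**4. Confounding.** A confounder must be associated with exposure. T is constant, so its covariance with SES and with severity is zero. Coefficients b2 and b3 can be estimated, but they describe which families improve.

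**5. Can the intercept stand in for the effect?** It reflects the proportion improving, which has no comparator. As an illustration, assume normal scores, equal means at both times and zero intervention effect:

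| Pre-post correlation (assumed) | Share with a reduction, all | Share with a reduction, baseline more than 0.5 SD above mean |
|---|---|---|
| 0.5 | 49.9% | 73.5% |
| 0.7 | 50.2% | 68.2% |
| 0.9 | 50.1% | 60.3% |

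About half improve with no effect at all, and more do when baseline burden is high. The article does not select caregivers on burden, so the last column shows regression to the mean as a mechanism and is not a forecast for this study.

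**The case against.** **Could another variable carry the exposure?** This is the best defence. Sessions and intensity can differ between children, several centres may be set up, and utilization will be recorded. But none is named in this model. Clinic or region is named only for the ANOVA, and every clinic delivers the intervention. Number of sessions follows the child's condition: "Treatment dose, intensity and sessions will be modified based on functional goals". A model of utilization would answer a question about amount received, not intervention versus none. What stands is that the analyst has a legitimate exposure to model if it is defined and reported as an association. A reader might infer that the analyst is bound to report a false effect; the text does not go that far.

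**Does Table 1 imply a second arm?** It has an allocation row, but no second group is described anywhere.

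**Is it only a label?** Largely, and that limits the damage. A reader might infer that the whole evaluation of the primary outcome fails. It does not: the pre-post comparison of scores is a separate analysis and can still be computed.

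**Is baseline burden wrongly left out?** A reader might infer this from the two covariates named. They are given as examples, and an article may leave the full list to a longer document. Nor is it settled which way leaving it out would bias the SES coefficient. If endline burden depends on SES only through baseline burden, omitting baseline creates an association. If SES shifts burden equally at both times, including baseline creates one. The documents favour neither.

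**Does the intercept's dependence on the reference category add to the case?** No. That is a matter of coding and goes away when covariates are centred. The objection to the intercept is the missing comparator.

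**Conclusion.** The point holds for the regression's stated aim. As described, the model cannot estimate the impact of the intervention: the coefficient is unidentified (4 columns, rank 3) at every sample size. The covariates cannot adjust for confounding of an effect that the model does not contain. This rests only on the single arm, treatment of every enrolled child, and an outcome defined as a before-after reduction, all of which the article states. It does not depend on details that an unseen analysis plan might supply, unless that plan adds a comparison group or a defined exposure, which would be a different analysis.

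No bias in an odds ratio can be put in numbers from the documents, and none is claimed. A reader might also infer that the pre-post change is then the effect of the centre. The design does not support that either, since maturation, time trends and regression to the mean remain in it.

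**What to change.** In the Statistical analysis section:

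1. Delete the claim that the logistic regression identifies the intervention's impact, and the claim that it controls for confounding.
2. Rename it *factors associated with reduction in caregiver burden*, and state that neither the intercept nor any coefficient is an effect of the centre.
3. Report the paired t0-to-t5 change in burden score with its 95% CI, described as an uncontrolled before-after change that may also reflect maturation, time trends and regression to the mean.
4. If an exposure that varies, such as clinic utilization, is added, define it in advance and report it as an association only, because sessions follow the child's functional goals.

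The cost is the rewording of one paragraph, with no new data, visits or software. The downside is that the study can no longer claim a confounder-adjusted effect of the centre.

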## Qualitative analysis

Parents of the children who received rehabilitation in the model clinic will be interviewed face to face to understand the impact of model outreach clinic in reducing their burden and improving the access and child care. The entire interview will be audio recorded with parental consent and will be analyzed using grounded theory analysis following which themes and subthemes will be derived.

## Discussion

The anticipated primary outcome of the research will focus on the influence of the model center on reducing the burden among caregivers of children with NDD in the adopted villages affiliated with SRM Institute of Science and Technology, situated in Kattankulathur. Moreover, alongside the dissemination of the research findings, it will facilitate the strategic development of specialized services and the provision of care, as well as the appropriate referral of patients to higher levels of healthcare as necessary.

The Indian government has initiated UBA Scheme for the upliftment of rural villages. The primary objective of the UBA scheme is to engage higher educational institutions in research and understanding the realities of these communities at grass root level to contribute to the development of the village.

SRMIST under UBA has signed a Memorandum of Understanding with the Tamil Nadu State Institute of Rural Development and Panchayat Raj (SIRD&PR). The aim of the MoU was aligned with nine Local Sustainable Developmental Goals (LSDG) which included healthy village and child friendly village.

This research tries to fulfil these objectives by involving health care professionals in village level care via which both hospitals will be benefited by understanding the realities and also the village will be uplifted by reducing disability and caregiver burden. Also, the establishment of local outreach centre will help reducing the time and travel burden of parents making sure that the child receives treatment to the maximum.

The findings of this investigation will yield essential data concerning the frequency of developmental irregularities and disabilities among preschool children in twelve adopted villages linked with SRM, located in Kattankulathur. This data has the potential to steer the formulation of suitable strategies and protocols for the early implementation of rehabilitative measures, thereby alleviating the burden of disability among preschool children.

Furthermore, this study can act as a blueprint for establishing similar centers in various regions within Tamil Nadu. The data gathered will serve as a compass for governmental bodies and healthcare agencies in devising pertinent strategies and protocols to mitigate the prevalence of disability among children in Tamil Nadu.

The effectiveness of specialized outreach clinics in rural locations has been established in improving patient outcomes by avoiding the requirement for referrals beyond the community (out-of-community care) and strengthening the continuity of care. Among the various frameworks available for delivering specialized care, outreach specialist clinics have exhibited scalability. [16, 24].

The establishment of a specialized outreach program for pediatric rehabilitation aims not only to enhance access but also to ensure the equitable dispersion of healthcare services and communal involvement. This initiative will not only bolster community engagement but also enhance awareness and motivation among neighboring villages and communities to actively partake in rehabilitation efforts by dispelling the associated stigma. [24].

The outcomes of this study strive to fulfill the exigency for substantiating the efficacy of outreach clinics in rural and underprivileged areas despite previous studies highlighting the dearth of robust research evidence in this domain. [16].

## Data Availability

No datasets were generated or analysed during the current study.

## Abbreviations

UBA: Unnat Bharat Abhiyan
SRMIST: SRM institute of science and technology
NDD: Neurodevelopmental disorder
ADHD: Attention deficit hyperactivity disorder
DCD: Developmental coordination disorder
ASQ: Ages and stages questionnaire
NFHS: National family health survey
